### Statistical considerations

#### Justification of sample size

Power for the three-arm trial was estimated based on an alpha of 0.025, which is a Bonferroni correction for multiple comparisons, given three treatment conditions with two planned contrasts. We assumed a 40% base rate in engagement in AUD treatment at 34-days post-discharge (primary outcome) following BNI based on our YAMCS post-discharge data and published reports from other hospital-based addiction medicine consult services [13]. A sample size of 450 (150 per condition) will provide adequate power (> 80%) to detect a 15% increase in engagement from the comparator treatment (BNI + MAUD or BNI + MAUD + CBT4CBT) at 34-days, consistent with a small to medium effect (delta = 0.34). With a sample size of 360 participants (120 per condition), we would have > 80% power to detect a 20% increase in engagement, consistent with a medium effect (delta = 0.46). Thus, with a randomized sample of 450, we will have adequate power to detect a medium effect on AUD treatment engagement, assuming a 20% loss of data at follow-up. This is based on experiences with similar populations at YNHH [65], as well as those in our prior outpatient treatment studies [34, 74, 76].

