
### Study aims and hypotheses

Among 450 hospitalized individuals with untreated moderate to severe AUD (by Diagnostic and Statistical Manual-5 [DSM-5] criteria), our aims are to evaluate the effectiveness of hospital-initiated BNI vs. BNI + MAUD vs. BNI + MAUD + CBT4CBT on AUD treatment engagement at 34 days (primary outcome) and 90 days post-discharge; changes in alcohol use by self-report and biomarker over the 90 day period; and (exploratory) health care utilization, including Emergency Department visits and hospital readmission (Aim 1). We hypothesize that BNI + MAUD + CBT4CBT will be more effective than BNI + MAUD, which will be more effective than BNI alone as evidenced by higher rates of AUD treatment engagement, and reductions in alcohol use and urgent and emergency healthcare utilization post-discharge.

We will explore whether the effectiveness of the interventions on AUD treatment engagement and alcohol use outcomes differs across and within racial and ethnic groups and by SDOH indicators that reflect sequalae of structural racism (Aim 2). We hypothesize that there will be no difference in treatment effectiveness by race or ethnicity after adjustment of confounders but there will be differences based on SDOH.

Consistent with our prior experiences [40], we will additionally conduct an implementation-focused process evaluation [21], involving process measures, a clinician and staff survey, in addition to obtaining measures of the amounts and unit costs of resources used to implement each intervention to patients as well as health care staff. Analyses of cost, cost effectiveness, possible cost-savings benefits from reduced use of health care following the intervention, and cost–benefit for each intervention will compare individual-level provider and patient costs, indices of cost-effectiveness, and indices of cost–benefit for the three intervention combinations, as well as intervention-level indices of incremental cost-effectiveness ratios (ICERs) [41, 42] (Aim 3).

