#### Statistical analyses

##### Primary and secondary outcomes

The primary objective of this analysis will be to determine if the proportion of participants with formal AUD treatment engagement (yes/no) at 34 days post-discharge differs among those randomized to BNI alone, BNI + MAUD, and BNI + MAUD + CBT4CBT in this diverse sample. The primary outcome (1a) of AUD treatment engagement is binary and we will use logistic regression with two planned contrasts to evaluate statistical significance of the differences in proportion of formal AUD treatment engagement (as verified through electronic medical record and/or contact with treatment facility). This statistical model will also be used to assess efficacy of study interventions on AUD treatment engagement at 90-days following randomization (1a). Secondary outcomes (1b) will include change in the self-reported percentage of heavy drinking days (PHDD) by month from the 30-day period prior to hospitalization (baseline) to the 34- and 90-day post-discharge timepoint, which will be evaluated with random effects regression statistical models. These models have several advantages in follow-up data from clinical trials of individuals who use substances, as they are less vulnerable than traditional MANOVA approaches to missing data [85, 86]. An additional secondary outcome will include change in biomarker PEth, which as a continuous outcome will be evaluated with a similar statistical approach. Given limited data on factors impacting PEth levels among hospitalized patients [87] and building from our own experiences [88], we will also evaluate the correlation between baseline self-reported alcohol use (in the 30-day period prior to hospitalization) and PEth levels (e.g., liver disease, hemoglobin [38]), factors associated with PEth levels adjusting for baseline self-reported alcohol use, and factors impacting change in PEth from baseline to follow-up. Exploratory outcomes of healthcare utilization, including rates and costs of emergency department visits and hospital readmissions during the 34- and 90-day post-discharge period will be evaluated with mixed model ANOVAs. Analysis of treatment effects on primary, secondary, and exploratory outcomes will include the following contrasts: *H1:* BNI + MAUD > BNI; BNI + MAUD + CBT4CBT > BNI + MAUD or BNI.

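### Testing the two planned primary contrasts by Holm instead of plain Bonferroni would raise the chance of winning both by about 8 to 16 points at the same 5% familywise error: a cheap improvement, not an error

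*Protocol article*

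**What the plan says.** The article's section on justification of sample size gives the basis of the power calculation: "alpha of 0.025, which is a Bonferroni correction for multiple comparisons, given three treatment conditions with two planned contrasts". The other planning inputs are:

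- Control rate: "We assumed a 40% base rate in engagement in AUD treatment at 34-days post-discharge (primary outcome) following BNI".
- First power statement: "A sample size of 450 (150 per condition) will provide adequate power (> 80%) to detect a 15% increase in engagement from the comparator treatment".
- Second power statement: "With a sample size of 360 participants (120 per condition), we would have > 80% power to detect a 20% increase in engagement". This is the 450 randomised less 20% loss.

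The section on primary and secondary outcomes says "we will use logistic regression with two planned contrasts to evaluate statistical significance". It gives no per-contrast threshold and no testing procedure. It lists BNI + MAUD against BNI as one contrast. For the three-component arm it leaves the comparator open, as either BNI + MAUD or BNI.

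The section on study aims and hypotheses states an ordering: "BNI + MAUD + CBT4CBT will be more effective than BNI + MAUD, which will be more effective than BNI alone".

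The article gives no engagement rate for the third arm, does not say whether tests are one- or two-sided, and gives no power for succeeding on both contrasts.

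**The concern.** The stated hypothesis has two steps, so the trial supports it in full only if both contrasts succeed. Under plain Bonferroni each contrast must reach 0.025 whatever the other shows. If one step is clear and the other has p = 0.03, the second is reported as not established. Holm would establish it under the same familywise error.

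The gain from stepping down lies entirely in the second rejection, which is what an ordering hypothesis needs. Without that rejection, the added value of MAUD or of CBT4CBT could be called unproven when a procedure with the same error guarantee would have shown it.

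**Working it through.** **Inputs from the article.** Alpha 0.05 / 2 = 0.025 per contrast; 40% engagement under BNI; increments of 15 or 20 points; 150 per arm, or 150 × 0.80 = 120 after loss.

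**Assumptions.** Two-sided tests. Third-arm rates of 70% and 80%, which apply the plan's increment a second time. Adjacent contrasts (arm 2 vs 1, arm 3 vs 2), with comparison of both active arms against BNI as the alternative reading.

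**Step 1: the plan's own power figures.** Power = Φ[(Δ − z·SE₀)/SE₁], with z = 2.2414 (two-sided 0.025), SE₀ = √(2p̄(1 − p̄)/n) and SE₁ = √([p₁(1 − p₁) + p₂(1 − p₂)]/n).

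- 40% vs 60%, n = 120: SE₀ = √(0.5/120) = 0.06455 and SE₁ = √(0.48/120) = 0.06325. Φ[(0.20 − 0.14468)/0.06325] = Φ(0.875) = 80.9%. The second power statement reproduces.
- 40% vs 55%, n = 150: SE₀ = √(2 × 0.475 × 0.525/150) = 0.05766 and SE₁ = √(0.4875/150) = 0.05701. Φ[(0.15 − 0.12924)/0.05701] = Φ(0.364) = 64.2%. The stated figure above 80% does not reproduce. One-sided at 0.025 the result is 74.2%.

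**Step 2: why Holm is at least as good.** Bonferroni rejects each contrast with p ≤ 0.025. Holm rejects the smaller p if it is ≤ 0.025, and then the other if it is ≤ 0.05. So every Bonferroni rejection is also a Holm rejection. Familywise error is at most 0.05 under any dependence:

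- If both nulls are true, a false rejection needs the smaller p ≤ 0.025, with probability at most 2 × 0.025.
- If one null is true, a false rejection needs that p ≤ 0.05.

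Simulated familywise error for Holm at 150 per arm was 4.7% under the global null and 4.6% with one null contrast and a 20-point effect on the other.

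**Step 3: chance of winning both contrasts.** 400,000 simulated trials per scenario, pooled two-proportion z-tests:

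| Engagement by arm | Analysed per arm | Contrasts | Bonferroni | Holm | Gain (points) |
|---|---|---|---|---|---|
| 40/55/70% | 150 | adjacent | 36.7% | 53.0% | 16.3 |
| 40/55/70% | 120 | adjacent | 22.0% | 35.0% | 13.0 |
| 40/60/80% | 120 | adjacent | 68.8% | 79.6% | 10.8 |
| 40/60/80% | 150 | adjacent | 83.6% | 91.3% | 7.7 |
| 40/55/55% | 150 | both vs BNI | 48.1% | 61.3% | 13.2 |

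**Step 4: analytic check of the first row.** Arm variances are 0.24/150, 0.2475/150 and 0.21/150, so the standardised means are 0.15/0.05701 = 2.631 and 0.15/0.05523 = 2.716. The correlation is −0.00165/(0.05701 × 0.05523) = −0.524. Let B(c₁, c₂) be the bivariate normal probability that both statistics exceed their cut-offs, with a = 2.2414 and b = 1.9600.

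- Bonferroni: B(a, a) = 0.3775.
- Holm: B(a, b) + B(b, a) − B(a, a) = 0.4515 + 0.4564 − 0.3775 = 0.5304.

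Both agree closely with the simulation.

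**Step 5: what does not change.** The chance of at least one win is the same under both rules, because the first rejection still needs 0.025. In the first row it is 63.8% + 67.8% − 36.7% = 94.9%. Single-contrast power in that row rises from 63.8% to 73.4% (BNI + MAUD vs BNI) and from 67.8% to 74.5% (three-component arm vs BNI + MAUD), still below 80%.

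**The case against.** **The 0.025 belongs to the power calculation.** The article does not state it as a decision rule, and the analysis section fixes no threshold. A reader might infer that each contrast is bound to 0.025 in the final analysis, but the article does not say so. An analysis plan that is not shown could already step down. This stands, and it limits the point to the only rule the article states. It does not remove the point, because that rule is named as Bonferroni and tied to the same two contrasts.

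**Bonferroni is valid and standard.** This stands: nothing here is a validity error.

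**If only the full ordering counted, no correction would be needed.** Each contrast could then be tested at 0.05, with power at least equal to Holm's (36.2% against 35.0% at 40/55/70% with 120 per arm). That is true, but the plan corrects for two contrasts, which implies that each may be claimed separately. Holm suits that aim.

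**The figures are conditional.** This stands. A reader might take 37% to 53% as the gain for this trial. It needs a third-arm rate that the article does not give, the adjacent reading of an open contrast, and no loss, although the article assumes 20% loss.

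**Holm is not wholly free.** This stands. The error for a single true null rises from 0.025 to about 0.04, and to about 0.05 when the other effect is very large. Simple 97.5% intervals can include no effect when the second contrast is rejected at a p between 0.025 and 0.05.

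**Conclusion.** The point holds as a cheap efficiency improvement. At the plan's effect sizes Holm adds about 8 to 16 points to the chance of winning both contrasts, within the same 5% familywise error and without more participants. The direction is the same under either reading of the second contrast. The size depends on two-sided tests and on assumed third-arm rates. With smaller effects the gain in points is smaller: at 40/50/60% with 120 per arm the chance goes only from 1.6% to 4.3%.

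A reader might infer that Bonferroni is why the trial would usually miss one of its two steps. The article's figures do not support that. At 40/60/80% with 120 per arm, Bonferroni wins both in 69% of trials. In the 15-point scenario the main cause is sample size: power per contrast is about 64% against the stated figure above 80%. Holm does not repair that shortfall; after 20% loss it still misses at least one step in 65% of trials (100 − 35).

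**What to change.** Add one sentence to the analysis section: the two planned contrasts on 34-day engagement are tested by Holm, the smaller p-value at 0.025 and, if that is rejected, the other at 0.05. Keep 0.025 as the planning alpha, since it is Holm's first step. If the analysis plan already steps down, say so.

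Make the change before outcomes are compared by arm. The article reports recruitment and follow-up as ongoing, and a later switch would look data-driven.

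Report 97.5% intervals for both contrasts whatever the test results, with a note that they do not correspond exactly to the Holm decision. That note and the one sentence are the whole cost: no rejection is lost and the sample size is unchanged. The power statement for a 15-point difference needs its own correction.

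### Power for a 15-point increase with 150 per arm at alpha 0.025 is about 64–65%, not above 80%

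*Protocol article*

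**What the plan says.** The section Justification of sample size in the protocol article fixes the inputs. The significance level is "an alpha of 0.025, which is a Bonferroni correction for multiple comparisons, given three treatment conditions with two planned contrasts". For the control condition: "We assumed a 40% base rate in engagement in AUD treatment at 34-days post-discharge", under BNI. It then makes two power statements:

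- "A sample size of 450 (150 per condition) will provide adequate power" (above 80%) "to detect a 15% increase in engagement from the comparator treatment", described as a small to medium effect with delta 0.34.
- With 360 participants (120 per condition), power is also above 80% for a 20% increase, described as a medium effect with delta 0.46.

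It concludes that 450 randomised participants suffice for a medium effect after 20% loss of data. Sidedness is not stated. The section Primary and secondary outcomes specifies logistic regression with two planned contrasts and writes them directionally: "BNI + MAUD > BNI; BNI + MAUD + CBT4CBT > BNI + MAUD or BNI". Allocation is 1:1:1 (Recruitment and randomization).

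**The concern.** The two power statements are hard to reconcile. At one alpha and one base rate, 120 per arm is said to give a little over 80% power for 20 points, and 150 per arm is said to do the same for 15 points. Required sample size grows roughly with the inverse square of the difference. Going from 20 to 15 points therefore multiplies it by about (20/15)² = 1.78, while 150/120 is only 1.25.

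The statement concerns the primary outcome. If it is wrong, a true 15-point benefit would be missed far more often than the article implies. A reader who takes the figure at face value could treat a non-significant contrast as good evidence against a 15-point effect. This matters most for adding CBT4CBT to BNI + MAUD, an incremental comparison in which a modest effect is plausible.

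**Working it through.** **Inputs (protocol article).** BNI rate p1 = 0.40; alpha 0.025 per contrast (0.05/2); 150 per arm, or 120 after 20% loss (150 × 0.8); binary outcome; pairwise contrasts. Two-sided testing is the base case because sidedness is not given.

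**Is 15% absolute or relative?** On the log-odds scale, delta = ln(OR) × √3/π.
- 40% to 55%: ln(OR) = 0.606, delta = 0.334, close to the stated 0.34.
- 40% to 46% (relative 15%): ln(OR) = 0.245, delta = 0.135.

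The increase is therefore absolute, 40% to 55%. The relative reading would give only about 12% power.

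**Formulas.** With d = p2 − p1 and SE1 = √[(p1(1−p1) + p2(1−p2))/n]:
- unpooled power = Φ(d/SE1 − z);
- pooled power = Φ((d − z·SE0)/SE1), where SE0 = √[2p̄(1−p̄)/n].

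For two-sided 0.025, z = 2.241.

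**The statement that reproduces: 40% vs 60%, n = 120.** SE1 = √(0.48/120) = 0.0632; d/SE1 = 3.162.
- Unpooled: Φ(3.162 − 2.241) = 0.821.
- Pooled: SE0 = √(2 × 0.25/120) = 0.0645; power 0.809.

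Both are just above 80%, as stated.

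**The statement that does not: 40% vs 55%, n = 150.** SE1 = √[(0.24 + 0.2475)/150] = 0.0570; d/SE1 = 2.631.
- Unpooled: Φ(2.631 − 2.241) = 0.652.
- Pooled: p̄ = 0.475, SE0 = 0.0577; power 0.642.
- Exact enumeration of the chi-square test: 0.638.
- Simulated logistic Wald contrast: 0.638.

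**Variations for 15 points**

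| Setting | Power |
|---|---|
| 150/arm, two-sided 0.025 | 64–65% |
| 150/arm, one-sided 0.025 (same as two-sided 0.05, no Bonferroni) | 74–75% |
| 150/arm, one-sided 0.05 (same as two-sided 0.10) | 83–84% |
| 120/arm, two-sided 0.025 | 53–55% |
| 120/arm, one-sided 0.025 | 63–65% |
| 55% vs 70%, 150/arm, two-sided 0.025 | 67–68% |
| 55% vs 70%, 120/arm, two-sided 0.025 | 56–57% |

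The last two rows illustrate the second contrast. The 55% for BNI + MAUD is an assumption (the first contrast achieving its 15 points); the article gives no rate for that arm as comparator.

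**What the design can detect.** The smallest increase over 40% with 80% power at two-sided 0.025 is 17.5 (unpooled) to 17.7 (pooled) points at 150 per arm, and 19.5 to 19.8 points at 120 per arm.

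**Size needed for 15 points at 80% power.** Unpooled: (2.241 + 0.842)² × 0.4875/0.0225 = 205.9, so 206 evaluable per arm. Pooled: 210.

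**The case against.** The strongest reply is that the sample size does not rest on the 15-point figure. The section's closing conclusion is about the medium effect after 20% loss, that is, 20 points with 120 per arm, and it is correct. This stands: the number randomised, the alpha and the analysis are untouched, and the error is confined to one sentence.

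Second, the article ties its 80% for 15 points to the full 450. The 53–55% after loss is therefore a consequence worth reporting, not a second misstatement. That is right.

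Third, there are routes above 80%. Besides one-sided 0.05, comparing one arm of 150 with two pooled arms (300) at one-sided 0.025 gives about 85% (78–79% two-sided). Treating delta 0.34 as a difference in means gives 83.8% at two-sided 0.05, but 75.9% at two-sided 0.025. Each route leaves the stated alpha, the pairwise contrast or the binary outcome, and none rescues BNI + MAUD against BNI at the stated level.

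Fourth, sidedness is open and the contrasts are directional. One-sided 0.025 still falls short of 80%, so the conclusion does not depend on this.

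Finally, the parenthesis naming the comparator treatment lists BNI + MAUD and BNI + MAUD + CBT4CBT. It may mean the arms whose increase is measured, in which case it is only loose wording. Read literally, it makes the three-component arm a comparator, which it is in no planned contrast. The arithmetic does not depend on it.

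**Conclusion.** The concern holds. On the article's own inputs, power for a 15-point increase over 40% with 150 per arm is about 64–65% at two-sided 0.025 and 74–75% at one-sided 0.025, against the stated figure of above 80%. With complete data, a true 15-point benefit on the first contrast would be missed in about 35% of trials (two-sided). If 20% of participants drop out of the analysis, it would be missed in about 46%. This rests on reading 15% as percentage points, which the stated delta supports, and on pairwise contrasts of a binary outcome. The choice of formula moves the result by about one to two points. The 20-point claim with 120 per arm is correct.

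**What to change.** Revise the paragraph under Justification of sample size as follows:

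- Remove the claim of above 80% power for a 15% increase.
- State that 450 randomised with 20% loss (120 evaluable per arm) gives about 80% power for an absolute difference of 20 percentage points from 40%, at two-sided 0.025.
- State that power for 15 percentage points is about 65% with no loss and about 54% with 20% loss.
- Write percentage points throughout and state the sidedness of the test.
- Name BNI as comparator for the first contrast and BNI + MAUD for the second. Give power for the second from its higher comparator rate, labelled as an assumption (from 55% to 70%: about 68% without loss, about 57% with 20% loss).

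The cost is one reworded paragraph and a less favourable published figure. No extra patients and no change to design or analysis are needed, provided 20 points is accepted as the target. Keeping 15 points as the target at 80% power would instead need about 206 to 210 evaluable per arm.

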#### Statistical analyses

##### Primary and secondary outcomes

The primary objective of this analysis will be to determine if the proportion of participants with formal AUD treatment engagement (yes/no) at 34 days post-discharge differs among those randomized to BNI alone, BNI + MAUD, and BNI + MAUD + CBT4CBT in this diverse sample. The primary outcome (1a) of AUD treatment engagement is binary and we will use logistic regression with two planned contrasts to evaluate statistical significance of the differences in proportion of formal AUD treatment engagement (as verified through electronic medical record and/or contact with treatment facility). This statistical model will also be used to assess efficacy of study interventions on AUD treatment engagement at 90-days following randomization (1a). Secondary outcomes (1b) will include change in the self-reported percentage of heavy drinking days (PHDD) by month from the 30-day period prior to hospitalization (baseline) to the 34- and 90-day post-discharge timepoint, which will be evaluated with random effects regression statistical models. These models have several advantages in follow-up data from clinical trials of individuals who use substances, as they are less vulnerable than traditional MANOVA approaches to missing data [85, 86]. An additional secondary outcome will include change in biomarker PEth, which as a continuous outcome will be evaluated with a similar statistical approach. Given limited data on factors impacting PEth levels among hospitalized patients [87] and building from our own experiences [88], we will also evaluate the correlation between baseline self-reported alcohol use (in the 30-day period prior to hospitalization) and PEth levels (e.g., liver disease, hemoglobin [38]), factors associated with PEth levels adjusting for baseline self-reported alcohol use, and factors impacting change in PEth from baseline to follow-up. Exploratory outcomes of healthcare utilization, including rates and costs of emergency department visits and hospital readmissions during the 34- and 90-day post-discharge period will be evaluated with mixed model ANOVAs. Analysis of treatment effects on primary, secondary, and exploratory outcomes will include the following contrasts: *H1:* BNI + MAUD > BNI; BNI + MAUD + CBT4CBT > BNI + MAUD or BNI.

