### Recruitment and randomization

In collaboration with frontline clinicians, nursing staff, and YAMCS and *Epic* reports, potentially eligible participants are identified based on: (1) frontline clinician and staff referral; (2) identified with a proactive daily *Epic* generated report as having a documented Clinical Institute Withdrawal Assessment (CIWA) for Alcohol score in the past 96 h, an AUDIT-C score ≥ 7 in the past 96 h, and/or an active AUD diagnosis on their problem list, and are hospitalized on a general medicine ward; (3) YAMCS team referral; and (4) recruitment handouts and flyers for patients admitted to the hospital. Upon confirmation from the primary care team that the patient is appropriate to approach for research, the research coordinator will approach the patient and obtain verbal permission to screen for eligibility. Individuals who have an AUDIT-C ≥ 7 will be assessed for presence of a moderate to severe AUD by the Alcohol Symptom Checklist[45, 46] followed by screening for ≥ 1 heavy drinking day, defined as any day of consumption of ≥ 5 standard drinks for men, and ≥ 4 standard drinks for women[47] in the 30 days prior to hospitalization. Individuals who are identified as meeting eligibility criteria, provide written informed consent to participate, and complete baseline assessments are randomized 1:1:1 using a computerized urn randomization program that balances probability of treatment condition based on: (1) race and ethnicity, (2) sex, (3) Spanish language preference, and (4) AUD severity [48, 49]. Randomized participants receive $75 gift card or a tablet computer (“tablet”) for completion of baseline assessments and an additional $50 gift card for completing each of the two follow-up assessments.

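### Allocation is balanced on four factors that the primary logistic model, as described, does not name; if they predict engagement, leaving them out costs some power

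*Protocol article*

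**What the plan says.** Protocol article, Recruitment and randomization: patients are "randomized 1:1:1 using a computerized urn randomization program that balances probability of treatment condition based on" four characteristics, namely race/ethnicity, sex, preference for Spanish and AUD severity.

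Protocol article, Primary and secondary outcomes: for 34-day engagement, "we will use logistic regression with two planned contrasts to evaluate statistical significance of the differences in proportion". No covariate is listed and none is ruled out. The same section does name an adjustment for the baseline PEth analyses, and the Aim 2 hypothesis (Study aims and hypotheses) mentions adjusting for confounders.

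Protocol article, Justification of sample size: "Power for the three-arm trial was estimated based on an alpha of 0.025, which is a Bonferroni correction for multiple comparisons". "We assumed a 40% base rate in engagement in AUD treatment at 34-days post-discharge (primary outcome) following BNI". "A sample size of 450 (150 per condition) will provide adequate power (> 80%) to detect a 15% increase in engagement". With 120 per arm, more than 80% power is stated for a 20-point increase.

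**The concern.** Balancing allocation on a factor that predicts the outcome removes part of the chance variation in the treatment difference. A model that omits the factor still counts that variation in its standard error. Intervals are then somewhat too wide, the test rejects a true null less often than its nominal level, and power is lost. Even under simple randomisation, a model without a strong predictor tests with less power than one that has it.

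The direction is conservative, so a false positive is not the worry. What is at stake is efficiency, in a trial with little margin. The recomputed power is well below the stated figure for 15 points and only just above 80% for 20 points after losses. The variables are already recorded, because the urn needs them.

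**Working it through.** **1. The plan's own power figures.** Inputs from Justification of sample size: 40% under BNI, alpha 0.025 per contrast, 150 or 120 per arm. Sidedness is not stated; I take two-sided, z = 2.2414. Pooled normal approximation:

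power = Φ{ [d√n − z√(2p̄q̄)] / √(p₁q₁ + p₂q₂) }

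- 150 per arm, 40% v 55%: (0.15 × 12.247 − 2.2414 × 0.7062) / 0.6982 = (1.8371 − 1.5829) / 0.6982 = 0.364, power 64.2%. One-sided 0.025 gives 74.2%. Neither reaches the stated 80%.
- 120 per arm, 40% v 60%: (0.20 × 10.954 − 2.2414 × 0.7071) / 0.6928 = (2.1909 − 1.5849) / 0.6928 = 0.875, power 80.9%. The stated figure reproduces.
- 120 per arm, 40% v 55%: (1.6432 − 1.5829) / 0.6982 = 0.086, power 53.4%.

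**2. Mechanism, as a rough bound.** Suppose the factors explain a share R² of outcome variance and allocation balances them perfectly. On a linear approximation, the model without them has true type I error 2Φ(−z/√(1 − R²)). For assumed R² = 0, 0.05, 0.10 and 0.20 this gives 2.5%, 2.1%, 1.8% and 1.2%. An urn balances only in probability, so its effect is smaller.

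**3. Simulation under urn allocation.** Three arms 1:1:1, urn on the four factors, Wald tests at two-sided 0.025, treatment-only model against treatment plus four factors. There were 4,000 replicates for N = 450 and 6,000 for N = 360. Two inputs are assumptions: the odds ratio per factor, because the article gives none, and the factor prevalences, guided in part by the Study context section.

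| OR per factor | N = 450, 40% v 55%: without → with | N = 360, 40% v 60%: without → with | Type I error without factors, two contrasts, N = 450 |
|---|---|---|---|
| 1.3 | 63.98 → 64.90% | 80.92 → 80.93% | 2.58%, 2.28% |
| 1.5 | 63.28 → 64.93% | 80.72 → 81.55% | 2.55%, 2.15% |
| 2.0 | 62.38 → 66.40% | 80.60 → 84.08% | 2.53%, 2.13% |
| 3.0 | 64.02 → 71.70% | 81.55 → 87.70% | 1.70%, 2.05% |

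Power gains at N = 450 are 0.9, 1.7, 4.0 and 7.7 points; at N = 360 they are 0.0, 0.8, 3.5 and 6.2. For the contrast of the third arm with the second, taken as 55% v 70% at N = 450, the gains are similar: about 0.6, 1.3, 4.5 and 7.8 points.

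Monte Carlo standard errors: √(0.64 × 0.36 / 4000) = 0.8 points for power at N = 450, √(0.81 × 0.19 / 6000) = 0.5 points at N = 360, and √(0.025 × 0.975 / 4000) = 0.25 points for type I error at N = 450. Up to odds ratio 2, type I error cannot be told apart from 2.5%. At odds ratio 3, the 1.70% lies about (2.5 − 1.7) / 0.25 = 3.2 standard errors below nominal.

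**4. Sensitivity to the allocation scheme.** A tighter minimisation scheme gives type I error of 1.7–2.7% at odds ratios 1.5–2 and 0.9–1.3% at 3. Strong conservatism therefore needs both tight balance and strong factors.

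**The case against.** **The article may simply not list the covariates.** This is the strongest objection, and it stands in part. A reader might infer that the primary model contains treatment alone. The text does not say so: it gives the model class and the contrasts, and a condensed article commonly leaves the covariate list to the analysis plan. Adjustment is named for other analyses in the article, which makes the silence noticeable but does not turn it into an exclusion. The point is therefore a prespecification to make or confirm.

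**The factors are not shown to be prognostic.** This also stands as to size. The Introduction says that treatment rates differ between racial and ethnic groups, and Limitations says that Spanish-only speakers receive the advocates' sessions through translation. These give some reason to expect association, but no strength. The severity factor is narrowed by enrolling only moderate to severe AUD. With no association there is nothing to lose.

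**Type I error is not simply below nominal.** Tight pairing on a strong prognostic score can bring it to about 1.2%, and a reader might carry that figure over. It does not describe an urn, under which the level stays near 2.5% up to odds ratio 2 per factor.

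None of this argues for leaving the factors out. In the simulated scenarios adjustment did not reduce power.

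**Conclusion.** The point holds in a limited form. The factors used to balance allocation are not named in the primary model as described. A model without them is valid and, if they predict engagement, less efficient. Under urn allocation the loss is about 0–2 points of power for weak factors, 3–4 at odds ratio 2 each and 6–8 at odds ratio 3. These sizes rest on assumed strengths and prevalences and on two-sided testing at 0.025. I am confident of the direction but not of the size.

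A reader might also infer that adjustment would rescue the trial's power. It would not. The contrast of 40% with 55% stays between about 65% and 72% at N = 450 with all four factors in the model. That shortfall arises in the sample size calculation and is a separate, larger matter.

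**What to change.** State before unblinded analysis, or confirm if the analysis plan already says so:

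1. The primary logistic model, its 90-day counterpart and the random effects models for heavy drinking days and PEth include the four urn factors as covariates, coded as in the randomisation program.
2. If Spanish-preference cells are sparse, that factor is combined with ethnicity. This may well happen: 13% of the source population described in Study context is Hispanic or Latino. Proportional enrolment, which is an assumption, would give 0.13 × 450 ≈ 59 such patients, or about 20 per arm, and those preferring Spanish would be fewer.
3. Each contrast is reported as a standardised (marginal) risk difference: average the predicted probabilities over the whole sample under each arm, subtract, and give an interval. The stated aim is a difference in proportions. An odds ratio is non-collapsible, so an adjusted odds ratio alone would answer a different question.

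Further baseline predictors, such as the readiness ruler, are optional.

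The cost is two or three sentences of text. No new data are needed, and fixing the covariates now avoids a post hoc choice. The power statement in Justification of sample size needs its own correction.
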